### Assessment of outcome

Dose sufficiencyThe short term effects of high dose vitamin D therapy will be assessed by conduct of the following assays and diagnostic tests:Renal and liver function tests (including estimated Glomerular Filtration Rate (eGFR) and urine calcium/creatinine ratio)Serum 25OHD levelsSerum corrected calcium, 24 hour urinary calcium excretion or urinary calcium to creatinine ratio.The scheduling of these assessments is found in Table 1.AdherencePatients will be asked to keep a diary to record their use of the study drug. These diaries will be reviewed four monthly at each patient follow-up visit.The study team will confirm adherence to the treatment regime by contacting study patients at interim time points during the treatment phase and also during clinic follow-up visits at 4, 8, 12, 16, 20 and 24 months. To help improve adherence, monthly SMS text messages will be sent to those patients with mobile phones, reminding them to take their study tablets.In the event of a missed dose, patients will be able to take the missed dose at the following clinic visit. Appropriate procedures will be established to facilitate this while ensuring maintenance of necessary “blindness” with respect to the intervention arm each participant is in.SafetyThe feasibility, safety and short term effects of high dose vitamin D therapy will be assessed by the conduct of the assays and diagnostic tests found in Table 3.

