**Discussion:**

Effective, non-toxic adjuvant therapy for high risk primary melanoma is not currently available. Favorable outcomes of this phase II study will form the basis for a multi-centre phase III study to assess whether the addition of oral high-dose vitamin D therapy in patients who have completed primary treatment for melanoma and are at high risk of recurrence will:prolong time to recurrence within 5 yearsimprove overall survival at 5 years andbe both safe and tolerable.

62 patients have been randomised since the study commenced in December 2010. Target accrual for the study has been met with 75 patients randomised between December 2010 and August 2014.

The Mel-D trial is conducted by the Australia and New Zealand Melanoma Trials Group (ANZMTG 02.09)

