### Intervention

MaterialsStudy medications will be provided under the Australian Therapeutic Goods Administration Clinical Trials Notification scheme. Patients randomised to the active treatment arm will receive Cal.D.Forte tablets containing 50,000 IU of cholecalciferol from API Consumer Brands New Zealand. Patients randomised to the placebo arm will receive placebo tablets from a batch prepared by API for an unrelated study and provided by that study’s coordinator, [name], of the Menzies School of Health Research, Darwin.Study drug administrationPatients will receive oral vitamin D (Cal.D.Forte) tablets containing 50,000 IU of cholecalciferol from API Consumer Brands New Zealand or matching placebo.Following confirmation of eligibility and randomisation, patients randomized to active treatment will receive 500,000 IU of cholecalciferol (Vitamin D3) orally (10 tablets to be administered by the study team during the initial baseline study visit).Thereafter, patients will self-administer 50,000 IU, 1 Cal.D.Forte tablet on the 1st day of each month following commencement of treatment, for a period of 23 months.

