### Sample size and randomisation

The design of the study is an optimal two-stage phase II trial using the approach of Simon [41]. Sample sizes are determined separately for the two cohorts. The two cohorts, those receiving vitamin D and those receiving placebo, will be analysed separately. Assuming a lower limit of efficacy of 48% and a regimen activity level of 68%, the study would proceed in two stages. In the first stage, if more than 7 patients with serum 25OHD less than 80 nmol/l are observed in the first 14 patients in the active arm, consideration will be given to either modifying the regimen or stopping the study due to inactivity.

Twenty-five patients (in a 2:1 randomisation) will be accrued to the placebo arm to allow adequate data to estimate concentration of serum 25OHD in an untreated cohort. Thus it is proposed to accrue a total of 75 patients into the study, 50 receiving vitamin D and 25 receiving placebo. These calculations are based on power of 80% with 95% confidence and allow for a modest dropout rate.

Patients will be centrally randomised by the Australian National Health and Medical Research Council (NHMRC) Clinical Trials Centre using a computerised interactive voice response system (IVRS). Patients will be stratified by gender.

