### Statistical methods

Analysis of primary endpointsThe percentage of patients achieving a serum 25OHD above 80 nmol/l at 12 and 24 months receiving treatment will be reported. Summary statistics of serum 25OHD concentrations will be reported for both groups at 12 and 24 months.Dose adherence will be reported as the percentage of dose taken compared to the prescribed monthly dose as calculated from the patient diary and study forms. A 95% confidence interval will be reported to check if the expected rate of 80% dosage of study tablets for the duration of the study protocol by all patients is obtained.Safety outcomes will be reported as the proportions of patients exceeding the following maxima, as well as summary statistics where appropriate.Analysis of secondary endpointsParticipation rate will be reported as the proportion of subjects eligible and invited to participate who agree to be randomised. A 95% confidence interval will be reported to check if the expected rate of 60% was obtained.Progression free survival will be displayed using Kaplan-Meier survival curves.

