## Discussion

### Feasibility

Initial accrual to the ANZMTG 02.09 Mel-D study was slow, however a number of strategies have recently worked well in the early identification of eligible patients. All histopathology reports from wide excisions of melanoma are checked by the clinical trials staff and potentially eligible study participants are identified. The melanoma surgeons are reminded about study eligibility criteria prior to that patient’s consultation. In addition, a one-page Mel-D trial synopsis detailing the inclusion and exclusion criteria has been placed in the surgical consulting rooms and frequent updates of the trial progress are reported at the MIA research meetings. The study is promoted regularly on the ANZMTG website, membership newsletter and at various meetings (including the Annual Scientific Research Meeting).

Approximately 50% of eligible patients have participated in the study. The target accrual of 75 patients has been achieved and 21 patients have completed the full 24 months of treatment and follow-up. However, 10 patients have developed recurrence and ceased the trial. Planning for a phase III trial is underway, to open to melanoma treatment sites outside the Melanoma Institute Australia.

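### Participation is defined on eligible patients but analysed on those eligible and invited, accrual is called met without its two-year limit, and the adherence formula has no timing condition

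*Protocol article*

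**What the plan says.** **Participation and accrual.** The Secondary endpoints section of the protocol article sets one joint criterion: 60% of eligible patients agree to take part, and 75 patients are accrued within two years. Objectives of the present trial and Accrual rate repeat the target of 75 in two years, and the former ties it to a single site. Statistical methods reports participation among patients who were both eligible and invited, and compares that rate, with a 95% confidence interval, with the same 60%.

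On what happened, the Feasibility section says: "Approximately 50% of eligible patients have participated in the study". It also says that accrual was slow at first. The Discussion part of the Abstract states that target accrual has been met, with "75 patients randomised between December 2010 and August 2014". Feasibility likewise says that the target of 75 has been achieved.

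**Adherence.** Primary endpoints requires more than 80% of the prescribed monthly dose. Statistical methods says: "Dose adherence will be reported as the percentage of dose taken compared to the prescribed monthly dose", from the diary and study forms. The Intervention section prescribes "1 Cal.D.Forte tablet on the 1st day of each month following commencement of treatment, for a period of 23 months". Under Assessment of outcome, adherence is checked at "clinic follow-up visits at 4, 8, 12, 16, 20 and 24 months", and: "In the event of a missed dose, patients will be able to take the missed dose at the following clinic visit". No section says whether a dose made up in this way counts as taken.

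**The concern.** A pilot hands its feasibility rates to the next trial, and the article says that phase III planning is under way.

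The two participation denominators answer different questions. Randomised over eligible says how many of the patients who could enter a phase III trial will do so. Randomised over eligible and invited says how often an invitation is accepted. Only the first matches the stated criterion, yet the second is set against the same 60%. The gap between them is the eligible patients who were never approached. This could matter here: Feasibility describes slow early accrual, followed by steps to identify eligible patients sooner and to remind surgeons of the criteria.

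Calling target accrual met is true of the count of 75 but leaves out the time limit that is part of the criterion.

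Adherence is a primary endpoint. The Vitamin D background (Raising 25OHD concentrations) gives good compliance as one reason for the monthly regimen. A pure quantity measure cannot tell a patient who follows the monthly schedule from one who regularly catches up at clinic.

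**Working it through.** **The article's own calculation.** The only calculated figure is the sample size: "These calculations are based on power of 80% with 95% confidence and allow for a modest dropout rate". An exact binomial search for the Simon optimal two-stage design with rates 48% and 68%, one-sided alpha 0.05 and power 0.80 gives 14 patients with a limit of 7 in stage one, and 46 patients with a limit of 27 overall (exact alpha 0.044, power 0.805). The 14 and the 7 appear in the article, and 46/(1 − 0.08) = 50 with an assumed 8% dropout (no figure is given). So the size reproduces. It concerns serum 25OHD only. The 60% and 80% limits are set targets with no calculation behind them.

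**Participation.** Let E be the eligible patients, I those of them who were invited (I ≤ E), and R those randomised. Then R/I ≥ R/E always.

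- R = 75 (Abstract). R/E is about 0.50 (Feasibility), so E is about 75/0.50 = 150. This is an assumption, as E is not given.
- R/E = 75/150 = 50.0%, Wilson 95% CI 42.1% to 57.9%, which excludes 60%.
- R/I reaches 60% when I ≤ 75/0.60 = 125, that is, when 150 − 125 = 25 or more were not invited (25/150 = 16.7%).

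| Invited, of 150 eligible | Randomised/invited | Wilson 95% CI |
|---|---|---|
| 150 | 50.0% | 42.1% to 57.9% |
| 140 | 53.6% | 45.3% to 61.6% |
| 130 | 57.7% | 49.1% to 65.8% |
| 125 | 60.0% | 51.2% to 68.2% |
| 110 | 68.2% | 59.0% to 76.1% |
| 100 | 75.0% | 65.7% to 82.5% |

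The share does not depend on the count: 0.50/0.60 = 83.3% invited is the turning point for any E. Since the 50% is approximate, take E = 136 (55.1%) and E = 167 (44.9%). The turning points become 125/136 = 91.9% and 125/167 = 74.9% invited. If the check were passed whenever the interval contains 60%, 10 uninvited patients out of 150 would be enough (the row for 140).

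**Accrual.** Planned: 75/24 = 3.1 a month. Observed: December 2010 to August 2014 is about 44 months, and 75/44 = 1.7 a month.

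**Adherence.** Take a patient prescribed all 23 monthly doses.

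- More than 80% means more than 0.80 × 23 = 18.4, so at least 19 doses: 19/23 = 82.6% passes and 18/23 = 78.3% fails.
- There are six visits. Assume one make-up dose per visit; the article states no limit.
- 13 on schedule: 13/23 = 56.5%. With make-ups, (13 + 6)/23 = 19/23 = 82.6%, a pass.
- 15 on schedule: 15/23 = 65.2%. With make-ups, 21/23 = 91.3%.
- 17 on schedule: 17/23 = 73.9%. With make-ups, 23/23 = 100%.
- If several doses could be made up at one visit, the total could reach 100% from any starting point.

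With visits four months apart, a made-up dose can be up to about four months late.

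**The case against.** **The article is open about recruitment.** Feasibility reports slow initial accrual and about 50% of eligible patients, which is the less favourable denominator. The Abstract gives the dates in the same sentence as the accrual claim. This stands. A reader might infer that the endpoints were built to overstate success; nothing in the article shows that.

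**The denominator cannot rescue the criterion.** A reader might also infer that recruitment could be declared successful by choosing the narrower denominator. It could not, because the criterion also requires 75 patients in two years and accrual took about 44 months. This stands too. What remains is that one threshold is attached to two different rates.

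**Agreeing may presuppose an invitation.** The wording of the criterion can be read that way, no count of invited patients is given, and Feasibility does not say that known eligible patients went unapproached. So the actual size of the difference is unknown. Its direction is not.

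**Scoring of make-up doses may be settled elsewhere.** The article permits a late dose and is silent on how it is scored; the full protocol or analysis plan may say. Counting a permitted dose is also a legitimate measure of quantity. It would therefore be too strong to say that made-up tablets count as monthly adherence. What the text supports is that the formula, as written, lets them count.

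**The data may be incomplete.** The histopathology check finds potentially eligible patients and is described as recent. Eligibility also needs blood tests, performance status and history. The diary is said to record use of the drug, without mention of dates. These limits stand and bear on the fix.

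**Conclusion.** The main point holds. Secondary endpoints and Statistical methods attach the same 60% to different denominators, and the analysed rate can only be equal to or above the defined one. At about 50% of eligible patients, it reaches 60% once one in six was not invited (25 of an assumed 150). The number invited is not given, so this shows what the rule allows, not what happened.

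The accrual statement needs a qualifier. On the article's own figures, neither the two-year limit nor the 60% was reached.

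The adherence point is secondary and conditional. If make-up doses count, and with one per visit, a patient with 57% of doses on schedule scores 83% and passes. This assumes scoring per patient and 23 prescribed doses; treatment interruptions under the safety procedures would change that number.

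**What to change.** 1. Reconcile Secondary endpoints with Statistical methods: for the 60% criterion, use all identified eligible patients as the denominator, as far as screening records allow, and show the eligible-and-invited rate beside it. State how eligibility was judged for patients not approached and from when screening was complete.
2. Qualify the accrual statements in the Abstract and in Feasibility: 75 patients in about 44 months with about 50% participation, against 75 in two years and 60%. Plan phase III on about 1.7 patients a month for this setting and on 50%.
3. Report on-schedule adherence beside total dose received, and say which of the two is set against 80%. The make-up rule itself need not change.

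The cost is mainly wording and one extra rate for each endpoint. The participation rate will be less favourable, and probably the adherence rate too. Early counts of eligible patients may be incomplete, and on-schedule scoring depends on the diaries or study forms showing when each dose was taken.

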### Sample size and randomisation

The design of the study is an optimal two-stage phase II trial using the approach of Simon [41]. Sample sizes are determined separately for the two cohorts. The two cohorts, those receiving vitamin D and those receiving placebo, will be analysed separately. Assuming a lower limit of efficacy of 48% and a regimen activity level of 68%, the study would proceed in two stages. In the first stage, if more than 7 patients with serum 25OHD less than 80 nmol/l are observed in the first 14 patients in the active arm, consideration will be given to either modifying the regimen or stopping the study due to inactivity.

Twenty-five patients (in a 2:1 randomisation) will be accrued to the placebo arm to allow adequate data to estimate concentration of serum 25OHD in an untreated cohort. Thus it is proposed to accrue a total of 75 patients into the study, 50 receiving vitamin D and 25 receiving placebo. These calculations are based on power of 80% with 95% confidence and allow for a modest dropout rate.

Patients will be centrally randomised by the Australian National Health and Medical Research Council (NHMRC) Clinical Trials Centre using a computerised interactive voice response system (IVRS). Patients will be stratified by gender.

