#### Primary endpoints

The primary endpoints will be met if the following criteria are achieved:Dose sufficiencyIf the majority of treated patients achieve a serum 25OHD of 80 nmol/l at both 12 and 24 months and the average serum 25OHD for treated patients is > 75 nmol/l at 12 and 24 monthsDose adherenceIf patients take > 80% of the prescribed monthly doseSafetyCalcium [40]■ If the mean serum calcium concentration in each patient is <2.75 mmol/L (11 mg/dL) over the course of the study.■ If there is no increase in the prevalence of hypercalcaemia relative to the baseline prevalence.■ If the urine calcium excretion in each patient is less than 7.5 mmol/24 h OR the mean urinary calcium-creatinine ratio in each patient is <1.0 (when calcium and creatinine are measured in mmol) over the course of the study.■ If there is no increase in the prevalence of hypercalciuria relative to the baseline prevalence.Kidney function■ If there is no greater than a 20% fall in the average estimated GFR [GFR = 186.3 × SerumCr^-1.154^ × age^-0.203^ × 1.212 (if patient is black) × 0.742 (if female) – MDRD formula (21)] over the course of the study.■ If the average eGFR at the end of the study is no more than 20% less in vitamin D treated patients than in placebo treated patients.Renal calculiIf no more than two episodes of renal calculus occurs in vitamin D treated patients during the course of the study.

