### Quality assurance

An independent Data Safety Monitoring Committee will periodically review the study for efficacy and safety. Efficacy will be reviewed after the first 14 patients in the active arm have completed 4 and 12 months of the vitamin D regimen. Safety data will be reviewed after 20 patients have completed 4 and 12 months of treatment and again when 35 patients have completed 12 months of treatment.

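### The stated 80% power and 95% confidence are not tied to the dose-sufficiency criterion: the 48% and 68% rates name no visit, and stage 1 cannot score the 12-and-24-month response

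*Protocol article*

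**What the plan says.** All references are to the Protocol article.

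- **Sample size and randomisation.** The active arm is analysed on its own with a Simon optimal two-stage design. The rates are given as "Assuming a lower limit of efficacy of 48% and a regimen activity level of 68%, the study would proceed in two stages". The stage-1 trigger is "if more than 7 patients with serum 25OHD less than 80 nmol/l are observed in the first 14 patients in the active arm"; if it is met, a change of regimen or a stop is considered. The plan is to "accrue a total of 75 patients into the study, 50 receiving vitamin D and 25 receiving placebo". On operating characteristics: "These calculations are based on power of 80% with 95% confidence and allow for a modest dropout rate". No visit is attached to the rates or to the stage-1 count, and no final cut-off is printed.
- **Quality assurance.** "Efficacy will be reviewed after the first 14 patients in the active arm have completed 4 and 12 months of the vitamin D regimen".
- **Primary endpoints, dose sufficiency.** A majority of treated patients must reach 80 nmol/l "at both 12 and 24 months", and mean 25OHD must exceed 75 nmol/l at 12 and 24 months.
- **Statistical methods.** The percentage above 80 nmol/l at 12 and 24 months is reported, with summary statistics.

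**The concern.** A Simon design takes one binary response per patient, scored in the same way in both stages, and its power belongs to that response and to its own final cut-off. Here the response that decides dose sufficiency includes a 24-month value. When the first 14 active patients are reviewed at 4 and 12 months, that value does not exist. At 4 months the 12-month value does not exist either. Stage 1 is therefore scored on something other than the dose-sufficiency response, and the final criterion is a simple majority rather than a Simon cut-off.

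Two decisions depend on this: whether to modify or stop the regimen after stage 1, and whether dose sufficiency, the first primary endpoint listed, supports moving to phase III. A reader who takes the 80% and 95% as properties of the dose-sufficiency verdict would be misinformed.

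**Working it through.** **Inputs from the protocol.** p0 = 0.48; p1 = 0.68; first stage 14; power 80%; 95% confidence; 50 active patients after an unquantified dropout allowance; success threshold a majority; visits 12 and 24 months.

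**Assumptions.** One-sided alpha of 0.05 (sidedness is not stated). Equal success rates at the two visits, with a latent-normal within-patient correlation of 0.5, 0.7 or 0.9 (no document gives one).

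**1. Reproducing the plan's figure.** For stage-1 bound r1 of n1 and final bound r of n,

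power(p) = Σ over x = r1+1 … n1 of Bin(x; n1, p) × P[Bin(n − n1, p) > r − x].

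The optimal design for 0.48 vs 0.68 is r1/n1 = 7/14 and r/n = 27/46, so success needs 28 or more of 46 (28/46 = 61%). Type I error is 0.0439 and power 0.805. With 8% dropout, 46/0.92 = 50, the printed active arm. Of the variants tried, only this one fits both 14 and 50: the minimax design has n1 = 20 and n = 40; the optimal design at alpha 0.025 has 17 and 59; at alpha 0.10 it has 14 and 33.

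(The printed trigger, more than 7 failures, means 6 or fewer successes, one step looser than 7/14. With 27/46 it gives alpha 0.051 and power 0.860. This does not affect what follows.)

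**2. The written majority rule, with 48% and 68% taken as both-visit rates.** Success is 26 or more of 50.

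- P[Bin(50, 0.68) ≥ 26] = 0.994
- P[Bin(50, 0.48) ≥ 26] = 0.335

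**3. The same rule, with 68% taken as a per-visit rate.** The both-visit rate is Φ2(c, c; ρ) with c = Φ⁻¹(0.68). Power is then computed at that rate.

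| Assumed correlation | Both-visit rate | Power, majority (≥26/50) | Power, Simon rule (7/14, 27/46) |
|---|---|---|---|
| 0.5 | 53% | 63% | 15% |
| 0.7 | 57% | 79% | 28% |
| 0.9 | 62% | 94% | 52% |

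The last column scores both stages on the both-visit response. At perfect agreement between visits the Simon figure returns to 80.5%.

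**4. Majority required at each visit separately.** Simulation with 50 patients, the same correlations, and 26 or more successes needed at 12 months and again at 24 months gives power of about 99% at a per-visit rate of 68%. The false-positive rate at 48% is about 16%, 18% and 22%.

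**5. When 80% would be right.** The majority rule at n = 50 has 80% power at a both-visit rate of about 57%, not at the printed 68%.

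The mean-above-75 nmol/l part cannot be evaluated, because no standard deviation is given. Steps 2 to 5 therefore concern the 80 nmol/l part only. As a further condition, the mean part can only lower these pass probabilities.

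**The case against.** The strongest reply is that nothing in the protocol says 48% and 68% are single-visit rates. If they are both-visit rates, the Simon rule keeps 80.5% power. It even rises to about 85–87% if stage 1 is scored on a 4-month value, under the same assumed correlations and equal per-visit rates. The 4- and 12-month reviews could simply be early looks at whatever values are available, and the stage-1 trigger is not binding. The wording on 12 and 24 months can also mean a majority at each visit. Finally, this is a pilot trial with descriptive reporting, and an article condenses its protocol.

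Much of this stands. A reader might infer that the design was sized on a single visit and that a regimen with 68% activity is therefore likely to be declared insufficient. The documents do not support that. The 15%, 28% and 52% figures need a final cut-off of 28 of 46 that the article does not print, applied to the both-visit response. Under the only cut-off that is written, the majority, the same regimen passes the 80 nmol/l part 63%, 79% or 94% of the time.

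What does not go away is the mismatch itself. Even on the most favourable reading, the majority rule does not have the stated 80% and 95%. Nor is this only a detail left to a fuller document: the article prints the rates, the stage-1 rule, the review times, the power and the success criterion, and they do not fit together.

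**Conclusion.** The point holds in a limited form. The stated power and confidence belong to one binary response per patient with success at 28 or more of 46. They are not those of the written dose-sufficiency criterion, except by coincidence. The stage-1 count, reviewed at 4 and 12 months, cannot be the 12-and-24-month response.

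The size depends on the reading. Power for the majority part is 99.4% with a 33.5% false-positive rate (both-visit rates), 63–94% (per-visit rates, both visits required of each patient), or about 99% with a 16–22% false-positive rate (a majority at each visit). The last two rest on an assumed correlation of 0.5 to 0.9 and equal rates at the two visits; all use 50 evaluable patients. Because the true figure may lie above or below 80%, neither a general loss of power nor likely failure can be claimed.

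**What to change.** Keep the sample size. Reconcile Primary endpoints, Sample size and randomisation, and Quality assurance by naming the one response to which 48% and 68% apply.

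- If it is 80 nmol/l at both 12 and 24 months in the same patient, say so and label the stage-1 count an early single-visit surrogate.
- If it is a single-visit response, name the visit, score it in the same way in both stages, and report the other visit with a confidence interval.

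In either case, state whether the majority is counted per patient across both visits or at each visit. Print the final success rule, and restate power and type I error for that rule.

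The cost is wording, plus stated figures that may look less favourable. No extra patients or samples are needed.

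### The printed first-stage trigger (more than 7 of 14 below 80 nmol/l) is one patient more lenient than the Simon optimal design the protocol names

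*Protocol article*

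**What the plan says.** All of the relevant text is in the protocol article, Sample size and randomisation.

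- Design: "The design of the study is an optimal two-stage phase II trial using the approach of Simon". The vitamin D and placebo cohorts are sized and analysed separately.
- Rates: "Assuming a lower limit of efficacy of 48% and a regimen activity level of 68" per cent.
- First-stage trigger: "if more than 7 patients with serum 25OHD less than 80 nmol/l are observed in the first 14 patients in the active arm".
- Action at the trigger: "consideration will be given to either modifying the regimen or stopping the study due to inactivity".
- Error rates: "These calculations are based on power of 80% with 95% confidence and allow for a modest dropout rate".
- Size: "a total of 75 patients into the study, 50 receiving vitamin D and 25 receiving placebo".

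The article prints neither the second-stage boundary nor the evaluable number before dropout. Quality assurance gives the timing of the efficacy review of the first 14 active patients (after 4 and after 12 months of the regimen) but does not restate the trigger. No other section corrects it.

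**The concern.** A Simon first stage is written r1/n1 and is acted on when r1 or fewer of n1 patients are successes. The protocol's rule counts failures (25OHD below 80 nmol/l). With n1 = 14 and r1 = 7, seven or fewer successes is the same as seven or more failures. The printed rule acts only above seven failures, which corresponds to r1 = 6. If the named design has r1 = 7, the printed threshold belongs to a different design.

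At stake is the only numerical efficacy threshold given for the interim review. A regimen at the 48% level, which the design treats as inadequate, would reach that threshold less often than the named design provides for.

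**Working it through.** **Inputs** (all from Sample size and randomisation): p0 = 0.48, p1 = 0.68, power 0.80, n1 = 14, 50 active patients including dropout. The 95% confidence is taken as alpha = 0.05. Sidedness is not stated; one-sided is assumed and tested in step 1.

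**Formulas.** For a design r1/n1, r/n:

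- Chance of reaching the first-stage trigger: PET(p) = P(X ≤ r1), X ~ Bin(n1, p).
- Chance of declaring the regimen active: Σ over x > r1 of P(X = x) · P(Y > r − x), Y ~ Bin(n − n1, p). This is alpha at p0 and power at p1.
- Expected number: EN(p0) = n1 + (1 − PET(p0)) · (n − n1).

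The optimal design minimises EN(p0) subject to alpha and power.

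**Step 1: reproduce the protocol's design.** Exhaustive exact-binomial search:

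| Variant | r1/n1 | r/n | alpha | power | EN(p0) |
|---|---|---|---|---|---|
| Optimal, one-sided 0.05 | 7/14 | 27/46 | 0.0439 | 0.805 | 24.8 |
| Next best by EN(p0), one-sided 0.05 | 9/17 | 28/48 | 0.0430 | 0.806 | 25.0 |
| Minimax, one-sided 0.05 | 10/20 | 24/40 | 0.0435 | 0.802 | 26.9 |
| Optimal, one-sided 0.025 | 9/17 | 35/59 | 0.0230 | 0.802 | 27.8 |

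Only the first row gives n1 = 14. It also gives the number 7, and 46/(1 − 0.08) = 50 matches the active arm with 8% dropout. The protocol says only "allow for a modest dropout rate", so 8% is inferred; 5% would give 49 and 10% would give 52.

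**Step 2: express both rules on the same scale.**

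| Rule | Failures of 14 | Successes of 14 | r1 |
|---|---|---|---|
| Named design | 7 or more | 7 or fewer | 7 |
| As printed | 8 or more | 6 or fewer | 6 |

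They differ only when exactly 7 of 14 succeed. At p = 0.48 that has probability 3432 × 0.48^7 × 0.52^7 = 0.207. At p = 0.68 it is 3432 × 0.68^7 × 0.32^7 = 0.079.

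**Step 3: chance of reaching the trigger at a single look.**

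| True success rate | As printed, P(X ≤ 6) | Named design, P(X ≤ 7) |
|---|---|---|
| 48% | 0.455 | 0.662 |
| 68% | 0.046 | 0.125 |

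**Step 4: could r1 = 6 of 14 be optimal?** No. The smallest total that meets both error rates in any two-stage design is 40 (the minimax row). With r1 = 6, n1 = 14 and n = 40, EN(p0) = 14 + (1 − 0.455) × 26 = 28.2, against 24.8 for 7/14. A larger n only raises it.

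**Step 5: whole-design consequences, conditional on the unprinted 27/46 boundary, on the trigger being acted on, and on accrual pausing at 14.**

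| | As printed (r1 = 6) | Named design (r1 = 7) |
|---|---|---|
| EN(p0) | 14 + 0.545 × 32 = 31.4 | 14 + 0.338 × 32 = 24.8 |
| alpha | 0.0509 | 0.0439 |
| power | 0.860 | 0.805 |

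**The case against.** **The trigger does not bind.** The text offers a consideration, and a committee reviewing the first 14 patients would see a 7-of-14 result under either rule. This stands. A reader might infer that an inadequate regimen is stopped 45% of the time instead of 66%; the document supports only the chance of prompting a deliberation.

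**A reader might infer that the 5% error rate is broken.** The document does not support that. The figure of 5.1% depends on 27/46, which is not printed. Other boundaries hold both error rates with r1 = 6: 24/40 gives alpha 4.4% and power 80.6%, and 27/45 gives 3.7% and 82.1%. The primary endpoint criteria and Statistical methods state no final Simon test, and a condensed article may leave the second-stage boundary to the full protocol.

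**A reader might infer that about 6.6 more active patients would be treated at the 48% level.** That needs accrual to halt at 14, and no pause is stated. Assume steady accrual at the planned 75 in 24 months with 2:1 allocation. The 14th active patient (21st overall) then enters at 21/75 × 24 = 6.7 months. About 22 active patients are enrolled by the 4-month review and 39 by the 12-month review. The difference shrinks to 0.207 × (46 − 22) = 5.0 or 0.207 × (46 − 39) = 1.4 patients. The two review times also mean that a single-look probability is not the overall chance of a trigger.

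**The cause is unknown.** Confusing successes with failures would explain the text exactly, since 14 − 7 = 7. So would a loose paraphrase of a correct full protocol. The article does not print r1, so the cause stays an inference.

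**Accrual is complete**, by the article's own account, so a correction can no longer limit enrolment. This lowers the practical benefit.

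None of these points reconciles the printed threshold with the named design.

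**Conclusion.** The point holds as an internal inconsistency. The stated inputs lead to 7/14 as the optimal first stage, and the printed trigger is that of r1 = 6, one patient more lenient. At a 48% success rate, the chance of reaching the trigger at one look is about 21 percentage points lower than the named design gives; at 68% it is about 8 points lower.

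This rests on one-sided 5% alpha, which is assumed because it alone among the variants tried reproduces the first-stage size. The expected-number, alpha and power comparisons carry the further conditions in step 5. Even under those conditions, alpha shifts by 0.7 points and power rises by about 5.5 points, so the weakness lies in early futility protection and not in error control.

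**What to change.** Reconcile the trial-level trigger with the named design in one of two ways.

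1. Print it as 7 or more of the first 14 active patients below 80 nmol/l. The cost is one number in the protocol and in any monitoring committee document that repeats it. The chance of flagging a regimen at the 68% level rises from 4.6% to 12.5%, which the 80% power of the 7/14, 27/46 design already absorbs.
2. If more than 7 is intended, drop the word optimal and state a final boundary computed for r1 = 6 with its exact operating characteristics. For example, requiring at least 31 successes of 50 gives alpha 3.1% and power 83%. Expected active N at 48%, if accrual paused at 14, would be 14 + 0.545 × 36 = 33.6.

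In either case, state that alpha is one-sided if it is. Because accrual is complete, the trial report should also say which threshold was applied at the review of the first 14 active patients.
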